#### Interviews

We will conduct semi-structured KI interviews (*N* = 300) at end-of-intervention and 6 months post-intervention to obtain supplemental data about organizational changes for evidence-based CVD prevention (implementation policies and practices) and influential inner and outer context events. The KI interview at end-of-intervention will also ask about acceptability of the implementation support received (implementation effectiveness). The KI interview 6 months post-intervention will ask about practice-level outcomes (innovation effectiveness).

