10-year CVD Risk^a^	Mean (SD), median (IQR) of individuals who had CVD risk calculated

^a^based on ACSVD

We will measure practice outcomes qualitatively by asking whether evidence-based CVD prevention improved the practice’s standing in a pay-for-performance program, provided them with maintenance of certification credits, improved their payments through the BCBS of NC sponsored Blue Quality Physicians Program, or made them more attractive for recruitment into ACOs/Shared Savings Programs and other global payment programs.

*Inner context* refers to structural, political, and cultural features of the practice that are directly related to experiences of patients and staff, as well as features of the larger organization (if any) with which a practice is associated [20]. We will capture inner context through our measures of practice capacity for QI, organizational readiness, and implementation climate. In addition, we will assess other structural features, such as practice type (see Table 7).

**Table 7 Tab7:** Inner context measures

Practice type	Solo, single-specialty, multispecialty (NAMCS-EMR Q11-13)
Degree of integration	Practice owned by physician/group, HMO, CHC, AMC, other hospital, other corp. (NAMCS-EMR Q22)
Practice size	Number of physicians (NAMCS-EMR Q12)
Practice staffing	Number of mid-level providers (NAMCS-EMR Q14)
Patient volume	Number of office visits in a normal week (NAMCS-EMR Q10)/per provider full time equivalent (FTE)
Payer mix	Percent patient care revenue from Medicare, Medicaid, private insurance, other (NAMCS-EMR Q23)
EMR capabilities	Number and use of computerized capabilities (NAMCS-EMR Q18a-Q18j)

Items from the 2010 National Ambulatory Medical Care Survey electronic medical records

*Outer context* refers to features of the economic, political, and social context within which an organization resides [20]. Through the KI survey, we will assess the perceived influence of external events using a 3-point Likert scale (no influence to significant influence). In KI interviews, we will explore qualitatively how events rated “2” (some influence) influenced the practice’s efforts to implement evidence-based CVD prevention processes of care.

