#### Supplemental analysis

We will explore the reasons why some practices benefited more than others by identifying themes about actions taken, missed opportunities, influential inner and outer contextual factors, and other situational factors.

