### Limitations

Recruiting and retaining a large number of practices to engage in a yearlong, comprehensive quality improvement effort poses significant challenges. Potential recruitment barriers include fear of financial risk, reluctance to share data, acquisition by larger health systems, and competing priorities. Potential retention barriers include loss of a key clinician, resignation of a practice manager, and financial difficulties. We will attempt to mitigate these barriers by using practice facilitation to help practice achieve other goals (e.g., PCMH recognition) or enhance billing for services. Also, CCNC and AHEC will leverage their strong relationships with hospitals and health systems to boost recruitment and prevent attrition.

Our stepped-wedge study design affords some control of the effects of secular trends and other factors unrelated to our comprehensive quality improvement strategy. We will supplement this by documenting and including in our statistical analysis temporal events that could affect the implementation and outcomes of the strategy. However, the effects of outer context factors can be challenging to measure and model.

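### The interview rule for outer-context events names only the middle rating of a 3-point scale, so events rated as significant are not named for qualitative follow-up

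*Protocol article*

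**What the plan says.** The Outer context paragraph under Measures sets up two steps. First, the key informant survey rates the "perceived influence of external events using a 3-point Likert scale (no influence to significant influence" being the two end anchors. Second, the key informant interviews "explore qualitatively how events rated “2” (some influence) influenced the practice’s efforts to implement" evidence-based processes of care. The numeric codes are not given, and the label of the middle category appears only in the second step.

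Two other places describe what the interview material is for. The Interviews section says it supplies supplemental data on organizational changes and on context events; the wording is "implementation policies and practices) and influential inner and outer context events", with no limit to one rating. The Supplemental analysis under Aim 4 looks for reasons why some practices gained more than others, and its themes include "influential inner and outer contextual factors, and other situational factors".

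Table 1 lists three sources for outer context: key informant survey, key informant interview and practice facilitator contact logs.

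**The concern.** A follow-up rule of this kind normally starts from some level of influence and takes everything at or above it. Here the rule names one rating, with a label that sits below the scale's upper anchor. An interviewer who follows it as written would ask about events of moderate influence and would have no instruction to ask about those the practice rated as significant.

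At stake is the qualitative account of how outside events helped or hindered implementation. The protocol wants that account in order to explain differences between practices, and the events rated highest are the ones for which an explanation is most useful.

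This is more than detail that a condensed article leaves to an interview guide. The article states a specific selection value, and that value does not fit the purpose it gives the interviews.

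**Working it through.** No arithmetic applies: the point depends on no sample size, effect size or error rate. The check sets the rule against the scale and then against the stated purpose of the interviews.

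**Step 1: the rule against the scale.** The inputs, all from the Outer context paragraph, are three categories, a lower anchor of no influence, an upper anchor of significant influence, and a rating of 2 labelled as some influence. There are two plausible codings:

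| Coding | Meaning of 2 | Does the label fit? | Category not named for follow-up |
|---|---|---|---|
| 1 = none, 2 = some, 3 = significant | middle category | yes | significant |
| 0 = none, 1 = some, 2 = significant | top category | no | some, if the number governs; significant, if the label governs |

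Number, label and anchors agree only in the first row, and there the top category is not selected. In the second row the sentence contradicts its own scale. Neither coding yields a rule that covers both influential categories.

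**Step 2: the rule against the purpose.** The Interviews section asks for influential context events. An event rated as having significant influence is the clearest case of one, so under the coding that fits, the rule is narrower than the purpose. The same holds for the Aim 4 Supplemental analysis, which looks for influential contextual factors. It does not name its data source, but identifying themes is qualitative work of the kind the interviews support.

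**Step 3: how far the effect reaches.**
- The survey rates the events before any selection for interview, so a rating of significant is recorded whatever the interview rule says.
- Table 1 also lists practice facilitator contact logs for outer context. The article's text on those logs describes only the frequency, duration and mode of contact, so the survey is the firmer of the two remaining sources.
- Model (1) handles secular trend with a spline in calendar time. The secondary analyses of Aims 1, 3 and 4 bring in contextual factors as effect modifiers. Nothing in those sections makes either step depend on which events were discussed at interview.

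**The case against.** The strongest reply is that the paragraph never says other ratings are excluded. Read with the Interviews section, it most likely means a rating of 2 or above, with the last words dropped in drafting. Deliberately skipping the strongest events would run against the protocol's own aims. This is a fair reading of intent, and it stands to the extent that the text cannot be said to exclude significant events outright. It does not repair the rule: if a threshold was meant, the sentence misstates it, and the correction is the same.

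A second reply is that the coding and the probes belong in the survey instrument and the interview guide, which are not shown. That would answer a complaint that the codes are missing. It does not answer a rule that is stated and does not fit.

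A reader might also infer more than the documents support:
- *That information on significant events is lost.* It is not. The survey records those ratings; at most, their qualitative elaboration at interview is affected.
- *That control of secular trends is weakened.* The Limitations section promises "documenting and including in our statistical analysis temporal events that could affect the implementation and outcomes of the strategy", but that concerns the statistical analysis and is not tied to the interview rule.
- *That the most influential events are missed in every case.* Under a 0 to 2 coding with the number governing, they are the ones kept.
- *That the share of events missed can be stated.* The article gives no distribution of ratings, so any percentage would be invented.

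**Conclusion.** The point holds as a misstated selection rule of minor weight. Taken literally, under the only coding that fits its label, the rule does not name the events rated most influential for qualitative follow-up, which conflicts with the purpose given in the Interviews section and with the Aim 4 Supplemental analysis. Under the alternative coding the label is wrong. The conclusion therefore does not depend on which coding was meant; the direction of the gap does.

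Its size cannot be expressed as a number from the article. The effect is confined to supplemental qualitative data on outer context. The primary outcomes, the statistical models, the handling of secular trend and the power figures are untouched.

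**What to change.** State the three codes with their labels, and word the interview rule by label: explore every event that the key informant rated as having at least some influence, that is, some or significant. Wording by label gives the right selection under either coding and brings the Outer context paragraph into line with the Interviews section. If the survey instrument or interview guide already covers both categories, only the sentence in the protocol needs correcting; otherwise the guide changes as well.

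The cost is one phrase, and slightly longer interviews in practices that report significant events. No outcome, model or sample size changes.

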### Data analysis

#### Aim 1: Evaluate the effect of primary care practice support on delivery of evidence-based CVD prevention

Our primary hypotheses are that primary care practice support will improve the percentage of patients in a practice: (a) with ischemic vascular disease who use aspirin or other antithrombotics; (b) with hypertension who have adequate blood pressure control; (c) with an LDL test performed who are prescribed a recommended dose of statin based on risk status; (d) who were screened for tobacco use and, if identified as a tobacco user, received cessation counseling and/or pharmacological therapy; and (e) who receive aspirin for primary prevention based on a 10-year CVD risk status. Our secondary hypotheses are as follows: (a) practice capacity for QI, organizational readiness to implement change, implementation climate, and contextual factors (inner and outer) will moderate the effect of primary care practice support on evidence-based CVD prevention; and (b) primary care practice support will reduce race-based disparities in evidence-based CVD prevention.

#### Statistical analysis

The statistical analysis of the primary outcomes for Aim 1 will be based on a generalized linear mixed model (GLMM) for longitudinal binomial data at the practice level. Allowing for the number of patients who are observed within a practice to vary across time, the models will be estimated by maximizing the pseudo-likelihood, specifying practices as clusters, and using empirical variance estimators. For example, the number of hypertensive patients whose blood pressure is under control *Y*_it_, out of *N*_it_ hypertensive patients, will follow a binomial (*N*_it_, *π*_it_) distribution where, conditional upon a practice-specific random intercept *b*_i0_ and slope *b*_i1_, π_it_ = *E*(*Y*_it_/*N*_it_|*b*_i0_,*b*_i1_) is the expected proportion of hypertensive patients whose blood pressure is controlled within the *i*-th practice in the *t*-th month; *t* = s_i_ (baseline), s_i_ + 3, s_i_ + 6, s_i_ +9, s_i_ + 12, s_i_ + 18 (6 month post-intervention follow-up), and for some practices s_i_ + 24 (12 month post-intervention follow-up). The GLMM is1$$ \mathrm{Logit}\left({\uppi}_{\mathrm{i}\mathrm{t}}\right) = {\beta}_0 + {b}_{\mathrm{i}0} + {\beta}_1{X}_{\mathrm{i}1} + {\beta}_2{X}_{\mathrm{i}2} + {\beta}_{12}{X}_{\mathrm{i}1}{X}_{\mathrm{i}2} + {g}_1\left({t}^{*};\uppsi \right) + {b}_{\mathrm{i}1}t + {g}_2\left(t;\uplambda \right){X}_{\mathrm{i}\mathrm{t}3} + {g}_3\left(t;\uptheta \right){X}_{\mathrm{i}\mathrm{t}4} $$where *X*_i1_ = 1 indicates east region and 0 for west region; *X*_i2_ = 1 indicates higher readiness and 0 for lower readiness stratum; *g*_t_(*t*^*^;ψ) is a smooth spline function of calendar time (*t*^*^) for the secular trend corresponding to the control condition with finite dimensional parameter ψ; *X*_it3_ = 1 indicates the active (12 months) intervention period versus 0 otherwise and *g*_2_(*t*; λ) is function for four piecewise conjoined linear segments each of 3 months duration with λ being the vector of slope parameters; *X*_it4_ = 1 is an indicator for the maintenance period versus 0 otherwise and *g*_3_(*t*;θ) is a function for two piecewise conjoined linear segments the first of 6 months duration to which all practices will contribute data and the second 6 months durations to which only a subset of practices will contribute data as determined by the stepped-wedge design. Finally, *b*_i0_ and *b*_i1_ are assumed to be bivariately normal random variables with respective variances *σ*_0_^2^ and *σ*_1_^2^ and covariance *σ*_01_. Primary interest is in the treatment effect describing the log odds of a randomly sampled patient in a practice having the outcome 12 months post-intervention relative to the log odds of a randomly sampled patient from the same practice having the outcome during the pre-intervention period; this log odds ratio is well-defined as a function of λ parameters. Finally, the average causal effect of 12 months of intervention will be calculated as the average difference in proportions, Σ_i_[E(*Y*_it_/*N*_it_|*b*_i0_,*b*_i1_,*t* = s_i_ + 12)—E(*Y*_it_/*N*_it_|*b*_i0_,*b*_i1_*t* = s_i_)]/300; a 95 % confidence interval will be determined by bootstrapping. The random coefficients logistic model (1) will be fitted using SAS Proc GLIMMIX.

The secondary hypotheses will (a) introduce practice capacity for QI, organizational readiness to change, implementation climate, and contextual factors as main effects and effect modifiers in model (1) and introduce race as a main effect and effect modifier to examine whether primary care practice support reduces race-based disparities in the use of evidence-based CVD prevention. Examination of race will require outcome data aggregated at the practice level to be broken out by race.

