### Statistical analysis

For the primary hypotheses, communication and shared decision-making are binomial outcomes derived from patient surveys administered at baseline (*t* = s_i_) and at the end of the intervention period (*t* = s_i_ + 12). The model to assess improvement in these outcomes is a simplification of model (1) because there are only two repeated outcomes:3$$ \mathrm{Logit}\left({\uppi}_{\mathrm{i}\mathrm{t}}\right) = {\beta}_0 + {b}_{\mathrm{i}0} + {\beta}_1{X}_{\mathrm{i}1} + {\beta}_2{X}_{\mathrm{i}2} + {\beta}_{12}{X}_{\mathrm{i}1}{X}_{\mathrm{i}2} + {g}_1\left({t}^{*};\uppsi \right) + {b}_{\mathrm{i}1}t + {\beta}_3{X}_{\mathrm{i}\mathrm{t}3} $$where *X*_it3_ = 1 if *t* = s_i_ + 12 (end-of-intervention period) and *X*_it3_ = 0 if *t* = s_i_ (baseline). Note that exp(*β*_3_) is the odds ratio of a positive response (e.g., always communicated well, involved them in shared decision-making a lot of the time) after 12 months of intervention relative to the odds of a positive response at baseline, controlling for secular trends via ψ. The average causal effect of 12 months of intervention versus the control condition will be calculated as the average difference in proportions as described for Aim 1.

For the secondary hypothesis, model (2) will apply to claims data for the percentage of patients (a) hospitalized for a cardiovascular disease-related condition and (b) hospitalized for a CVD-related condition or died. For these outcomes, *X*_it3_ = 1 if *t* = s_i_ + 18 (6 months post-intervention) and *X*_it3_ = 0 if *t* = s_i_ (baseline). To assess whether primary care practice support decreases race-based disparities in these outcomes, the binomial data will be obtained for each race and practice and time point. Other facility-level patient outcomes are given in Table 4. Model (3) will be fitted to all binomial outcomes (e. g., percentage of patients…) using SAS Proc GLIMMIX. For continuous outcomes (e.g., a 10-year CVD Risk), an identity link function leading to a linear model fitted with SAS PROC MIXED will be used with variance weight 1/*N*_it_ where *N*_it_ is the observed number of patients in the *i*-th practice at the *t*-th month.

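### The Aim 1 average causal effect is a before-after difference, so it counts the secular trend as intervention effect

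*Protocol article*

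**What the plan says.** In the Aim 1 statistical analysis, model (1) is a logistic mixed model with a term g1 that "is a smooth spline function of calendar time" (t*), included "for the secular trend corresponding to the control condition with finite dimensional parameter ψ". The intervention enters through g2, with slope parameters λ. Two summaries of the 12-month effect follow.

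- A log odds ratio, named as the quantity of primary interest: "this log odds ratio is well-defined as a function of λ parameters".
- A difference in proportions: "Finally, the average causal effect of 12 months of intervention will be calculated as the average difference in proportions", with the formula "Σ_i_[E(*Y*_it_/*N*_it_|*b*_i0_,*b*_i1_,*t* = s_i_ + 12)—E(*Y*_it_/*N*_it_|*b*_i0_,*b*_i1_*t* = s_i_)]/300" and a bootstrap 95% interval.

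The Aim 2 statistical analysis applies the same calculation to communication and shared decision-making: "The average causal effect of 12 months of intervention versus the control condition will be calculated" as for Aim 1. The Limitations section says: "Our stepped-wedge study design affords some control of the effects of secular trends".

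**The concern.** Both terms of the formula describe the same practice, 12 months apart. Neither describes the practice at month s_i + 12 without the intervention. The result is a before-after change, yet Aim 1 labels it causal and Aim 2 describes it as a comparison with control.

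The two summaries of one effect therefore answer different questions: the odds ratio removes the calendar trend and the difference in proportions keeps it. They could disagree, and the absolute difference is the figure that is easiest to quote. A trend is plausible. The Background describes a national campaign on the same ABCS measures, launched in 2011 with a 2017 target, and the Trial status section puts the first intervention start in January 2016. The planning work could not have exposed the problem, because power model (2) assumes no temporal trend.

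**Working it through.** **1. Substitute model (1) into the formula.** The region and readiness terms and b_i0 cancel on the logit scale, leaving

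logit π(s_i + 12) − logit π(s_i) = g2(12; λ) + [g1 at s_i + 12 − g1 at s_i] + 12·b_i1.

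Setting g2 = 0 (no intervention effect) leaves the calendar-time change and the practice's own drift. The formula is then the average change under control.

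**2. Can calendar time be standing still?** The Research design section gives starts s_i at study months 9, 11, 12, 14 or 16, and model (2) uses (t − s_i)/12 as elapsed time. So t is study time, and t* advances 12 months when t does.

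**3. Reproduce the planning figure.** From the Aim 1 power section, β0 = 0.50 gives expit(0.50) = 62.2%, matching the stated 62%. With β3 = 0.05, expit(0.55) = 63.4%, a gain of 1.2 points for a low-readiness practice with random effects at zero.

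**4. Size of the error.** Inputs from the same section: β0 = 0.50, β2 = 0.05, variances 0.42 and 0.32, covariance −0.15. Assumptions: random slope scaled per 12 months from s_i, half the practices high-readiness, and the secular logit change shown. Averages over 4 million simulated practices, in percentage points:

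| Assumed 12-month secular change (logit) | Formula as written, β3 = 0 | Formula as written, β3 = 0.05 | Same-month contrast, β3 = 0.05 |
|---|---|---|---|
| −0.05 | −1.11 | −0.04 | 1.08 |
| 0 | −0.05 | 1.03 | 1.07 |
| 0.025 | 0.50 | 1.56 | 1.07 |
| 0.05 | 1.04 | 2.07 | 1.06 |
| 0.10 | 2.09 | 3.13 | 1.05 |
| 0.20 | 4.16 | 5.20 | 1.02 |

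The same-month contrast compares g2 on with g2 off at s_i + 12. It barely moves with the trend and is exactly 0 when β3 = 0. The row with no secular change shows that the drift term contributes only about −0.05 points on average.

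**5. Consequence for the interval.** Null trials were simulated with 300 practices, 1200 patients each, the same variance components and no intervention effect. The observed before-after difference stood in for the fitted formula. Runs of 2,000 and 4,000 trials per scenario agreed closely:

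| Assumed secular gain per year (points) | Mean estimate (points) | 95% interval excludes zero |
|---|---|---|
| 0 | about 0 | 5% |
| 1 | 0.9 | 22–25% |
| 2 | 1.8 | 71–74% |
| 3 | 2.7 | 96–97% |

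Check by hand: the simulated standard error is about 0.72 points. The shifts are then 0.9/0.72 = 1.25, 1.8/0.72 = 2.5 and 2.7/0.72 = 3.75 standard errors. The chance of exceeding 1.96 is P(Z > 0.71) = 24%, P(Z > −0.54) = 71% and P(Z > −1.79) = 96%.

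**The case against.** The strongest reply is that this is a companion summary. The article places primary interest in the log odds ratio, which excludes g1, and the Aim 2 odds ratio is likewise adjusted through ψ. No hypothesis test is attached to the difference in proportions. This stands: the rates above are not type I error rates of the primary analysis. It does not rescue the formula, which is still labelled causal and given a confidence interval.

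A second reply is that the formula conditions on t and never mentions t*, so the authors may have meant calendar time to be fixed. The label causal and the reference to control suggest that intent. The text does not say so, however, and calendar time moves with t within a practice. If that was the intent, the formula still needs correcting.

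Third, the secular rates and the per-year scaling of the random slope are assumptions. That is true, so the figures are illustrations. The algebra in step 1 needs neither.

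Fourth, the replacement depends on the model. All practices have started by month 16, so at s_i + 12 (months 21 to 28) none is still in the control condition. This stands too, but the primary odds ratio relies on the same separation of g1 from g2.

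**Conclusion.** The formula is wrong as written for Aim 1, and by reference for Aim 2. It estimates the intervention effect plus the secular change over 12 months, and equals the intended effect only when that change is essentially zero. The bias follows the trend: a rising trend inflates the result and a falling one can hide a real effect. Against a planning effect of about 1.0 to 1.2 points, a secular logit rise of 0.05 roughly doubles the reported figure, and a fall of 0.05 cancels it. These sizes rest on assumed trends, on the article's planning values and on a random slope scaled per year. The primary log odds ratio is not affected, and the practice-drift term is immaterial on average.

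**What to change.** Define the effect in Aim 1 as the average over practices of expit{η_i(s_i + 12) with g2 included} minus expit{η_i(s_i + 12) with g2 set to 0}. Use the same g1 (calendar time at s_i + 12) and the same b_i0 and b_i1 in both terms. In Aim 2, do the same with β3 included and set to 0. Obtain the interval by resampling whole practices and refitting the model. State that the no-intervention term comes from the model, since no practice is still a control at that time. If the present quantity is kept, call it an unadjusted before-after change.

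The cost is one formula in each of two sections and a short post-fit calculation, with no new data. The interval should be expected to widen, because it will carry the uncertainty in separating trend from intervention. Its width has not been calculated here.

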#### Statistical analysis

A random coefficients linear mixed model will be applied to the KDIS based on practice facilitator ratings collected monthly throughout the intervention period:4$$ E\left({Y}_{\mathrm{i}\mathrm{t}}\Big|\ {b}_{\mathrm{i}0},\ {b}_{\mathrm{i}1}\right) = {\beta}_0 + {b}_{\mathrm{i}0} + {\beta}_1{X}_{\mathrm{i}1} + {\beta}_2{X}_{\mathrm{i}2} + {\beta}_{12}{X}_{\mathrm{i}1}{X}_{\mathrm{i}2} + {g}_1\left({t}^{*};\uppsi \right) + {b}_{\mathrm{i}1}t + {g}_2\left(t;\uplambda \right)\ {X}_{\mathrm{i}\mathrm{t}3} $$where the explanatory variables and parameters are defined as in model (1). In particular, *X*_it3_ = 1 for all *t* = s_i_ + 1,…,s_i_ + 12, and *g*_2_(*t*; λ) is function for four piecewise conjoined linear segments each of 3 months duration in the intervention period with λ being the vector of slope parameters, which we expect to be positive indicating an increase in the number of clinical practice and office system changes with an increase in the amount of implementation support. The main hypothesis is an overall positive change in expected outcome between 12 months post-intervention and 1 month post-intervention. The first secondary hypothesis is that primary care practice support intensity (with *X*_it3_ re-defined and scaled as a continuous measure ranging from 0 to 1) will be positively associated with the KDIS scale *Y*_it_. The second secondary hypothesis will assess practice capacity for QI, organizational readiness to implement change, and contextual factors as effect modifiers on the rates of implementation given by *g*_2_(*t*; λ).

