#### Statistical analysis

We will analyze adaptive reserve and change process capability with a linear mixed model applied to the measures collected at baseline (*t* = s_i_), at the end of the intervention period (*t* = s_i_ + 12), and, for the early enrolled practices, at 6 months post-intervention (*t* = s_i_ + 18). The model to assess improvement in these outcomes is a simplification of model (1) because there are only two repeated outcomes:6$$ E\left({Y}_{\mathrm{i}\mathrm{t}}\Big|\ {b}_{\mathrm{i}0,}{b}_{\mathrm{i}1}\right) = {\beta}_0 + {b}_{\mathrm{i}0} + {\beta}_1{X}_{\mathrm{i}1} + {\beta}_2{X}_{\mathrm{i}2} + {\beta}_{12}{X}_{\mathrm{i}1}{X}_{\mathrm{i}2} + {g}_1\left({t}^{*};\uppsi \right) + {b}_{\mathrm{i}1}t + {\beta}_3{X}_{\mathrm{i}\mathrm{t}3}+{\beta}_4{X}_{\mathrm{i}\mathrm{t}4} $$where *X*_it3_ = 1 if *t* = s_i_ + 12 (end-of-intervention period) and *X*_it3_ = 0 otherwise; *X*_it4_ = 1 if *t* = s_i_ + 18 (6 months post-intervention) and baseline is the reference time period. Other assumptions are as in model (4). Primary interest is in *β*_3_, the difference in mean measure between baseline and end-of-intervention period.

In secondary analyses, contextual factors will be examined as additional main effects and as statistical interactions with *X*_it3_ in order to assess whether there are effect modifiers for the effect of primary care practice support on practice capacity to implement future evidence-based clinical guidelines. To test the hypothesis that primary care practice support generated additional positive practice outcomes, we will calculate 95 % confidence intervals for proportions of practices reporting positive outcomes, both overall and stratified by practice characteristics (inner context). We will also use logistic regression to ascertain whether additional positive outcomes varied as a function of primary care practice support intensity, KDIS scores, ABCS measures, and inner context variables.

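### The race-disparity analysis gives all races one secular trend, so any background change in the disparity is counted as an effect of practice support

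*Protocol article*

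**What the plan says.** In Aim 1, Statistical analysis, model (1) contains one calendar-time function, g1(t*;ψ). It "is a smooth spline function of calendar time" and stands "for the secular trend corresponding to the control condition with finite dimensional parameter ψ". The model also has a practice random intercept and a practice random slope. Neither these nor g1 is indexed by race. The support effect enters through g2, four joined three-month segments, and of the 12-month effect the article says "this log odds ratio is well-defined as a function of λ parameters".

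The secondary analysis of race is described in words only: it will "introduce race as a main effect and effect modifier to examine whether primary care practice support reduces race-based disparities". On the data it says "Examination of race will require outcome data aggregated at the practice level to be broken out by race".

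The article shows elsewhere what it means by effect modification. In Aim 3, capacity, readiness and context are assessed ("contextual factors as effect modifiers on the rates of implementation given by" g2). In Aim 4, contextual factors enter "as statistical interactions with *X*_it3_ in order to assess whether there are effect modifiers". Both are interactions with the intervention term, not with calendar time.

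In Aim 2, Statistical analysis, the plan is: "To assess whether primary care practice support decreases race-based disparities in these outcomes, the binomial data will be obtained for each race and practice and", and the sentence closes by naming each measurement occasion. That paragraph first assigns model (2) to the claims outcomes and later says model (3) is fitted to all binomial outcomes. Model (2) has no trend term; model (3) has a common g1.

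**The concern.** The hypothesis is causal: support will reduce disparities. The Limitations section relies on the stepped wedge for some control of secular trends. For the overall effect, g1 is the term that provides it. For the race contrast, as the model is written, nothing does. The model assumes that without support the disparity would have stayed constant over calendar time. If it was already narrowing or widening across the state, the race × support term would report that movement as an effect of support. Practice denominators are large, so the interval is tight and a small drift is enough.

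**Working it through.** **Step 1: what the race contrast contains.** Write the logit for race r in practice i at time t under model (1) with race added as described. The intercept, region and stratum terms, g1(t*), b_i0 and b_i1·t are the same for both races. Subtracting within a practice leaves

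disparity_i(t) = race main effect + race × g2 (+ race × g3 in maintenance).

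The visits are s_i, +3, +6, +9, +12 and +18, and only s_i precedes the intervention. With segments joined at 3, 6 and 9 months, g2 has a free value at each quarterly visit. Race × g2 at 12 months is therefore the mean of disparity(s_i + 12) − disparity(s_i). If the disparity drifts by δ over 12 months for outside reasons, the estimate is δ when support does nothing to it.

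**Step 2: inputs.** The article gives no figure for this test, so there is none to reproduce.
- From the article: 300 practices; starts at months 9, 11, 12 (50 practices each) and 14, 16 (75 each); 1200 patients per practice (the lower planning value); 62% baseline control; two-sided α of 0.05.
- Assumed: the state race mix (72% white, 22% black, Study setting) holds within practices; the 62% rate applies to both races in the hand calculation; drift δ; τ, the between-practice SD of the 12-month change in disparity; and the between-practice SD of the disparity itself.

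**Step 3: standard error as planned.** Denominators are 1200 × 0.22 = 264 and 1200 × 0.72 = 864, and p(1−p) = 0.62 × 0.38 = 0.2356.

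Variance of one logit disparity = 1/(264 × 0.2356) + 1/(864 × 0.2356) = 0.0161 + 0.0049 = 0.0210. Over two time points this is 0.0420.

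SE = √[(0.0420 + τ²)/300]; rejection ≈ Φ(δ/SE − 1.96).

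| τ | SE | δ = 0.025 | δ = 0.05 |
|---|---|---|---|
| 0 | 0.0118 | 56% | 99% |
| 0.1 | 0.0132 | 48% | 97% |
| 0.2 | 0.0165 | 33% | 86% |
| √0.05 | 0.0175 | 30% | 81% |

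On the proportion scale, 0.025 × 0.2356 ≈ 0.6 points and 0.05 × 0.2356 ≈ 1.2 points. At δ = 0.10 rejection is essentially 100%; at δ = 0 it is 5%.

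**Step 4: cross-checks.** Generalized least squares on the full two-race model, with the planning random-effect variances, returns estimates of exactly 0.025, 0.050 and 0.100 for those drifts. Rejection is 57% and 99% at τ = 0 and 30% and 82% at τ² = 0.05 for the first two drifts. Giving g1 1, 3 or 5 degrees of freedom changes nothing. Simulated race-specific binomial counts give 25–36% and 77–83% for τ of 0.1 to 0.2. A quadratic drift with a mean 12-month change of 0.041 also transfers in full (estimate 0.041).

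**Step 5: with a race-specific trend.** Adding race × linear calendar time returns 0.000 and 5% rejection under linear drift. The term is estimable because starts run from month 9 to month 16. The SE, for τ of 0.1 to 0.2, depends on the between-practice SD of the disparity:

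| SD of disparity | SE with race × time |
|---|---|
| 0 | 0.026–0.031 |
| 0.1 | 0.038–0.042 |
| 0.2 | 0.062–0.065 |
| 0.3 | 0.089–0.091 |

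The planned model gives 0.013–0.017. Adding race × stratum as well gives about 0.05 to 0.19 over the same range. That term matters because start month is tied to stratum (months 9–12 against 14–16) and randomization is only within stratum. Without it, a difference in disparity between strata can pass for a trend.

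**The case against.** The strongest reply is that the article never says in words that the trend is common to all races. It gives one sentence and no equation for the race model, and an analysis plan not shown could add race × g1. That is fair as a limit on certainty. But the article does state a specification: a written model with an unindexed trend, plus two named race terms, the second of which it uses in Aims 3 and 4 for interaction with the intervention. Read as written, it gives the wrong answer to a named hypothesis, which is more than an omitted detail.

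A second reply is that the size rests on inputs the documents lack. That stands for the rejection rates and the precision cost, which is why both are given as ranges. The full transfer of drift does not depend on those inputs.

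Third, the fix may leave an interval too wide to use, so this is a trade of bias against variance. That is also true, but the planned precision comes from assuming away the drift.

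Three stronger readings are tempting and not supported:
- A reader might extend the point to the other moderators in the same paragraph. Those are practice-level variables with no within-practice contrast that cancels g1, and the problem has not been shown for them.
- A reader might say the Aim 2 claims analysis has no trend term at all. Its text names both model (2) and model (3), so that is not settled; the race contrast is uncontrolled under either.
- A reader might infer that disparities really are drifting. The documents give no information on that.

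**Conclusion.** The concern holds for the Aim 1 race analysis and, under either model named, for the Aim 2 claims analysis by race. As specified, race × support at 12 months measures how the disparity changed from before to after, not what support did to it. The transfer of background drift is complete for the linear and quadratic forms checked. False rejection of roughly 25–57% at 0.025 logit per year and 77–99% at 0.05 depends on the assumed drift, race mix and between-practice variation. The hypotheses are secondary, the overall support effect is not touched by this argument, and the article's wording leaves some room for an unseen plan to have dealt with it. The change is worth making before any public claim that support reduced racial disparities.

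**What to change.** In the race analyses of Aims 1 and 2:
- Add race × g1(t*), or at least race × linear calendar time, and race × X_i2. The linear version removes linear drift but only most of a curved one.
- Base any claim that support reduced disparities on the race × support contrast from that model: race × g2 at 12 months in Aim 1, and race × X_it3 in Aim 2.
- Report the model without these terms only as change in disparity over time.
- Reconcile the Aim 2 text on whether model (2) or model (3) applies to the claims outcomes.

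No new data are needed. The cost is precision: the SE rises about 2 to 7 times with race × time (0.026/0.013 = 2.0; 0.089/0.013 = 6.8), and to about 0.05–0.19 logit with race × stratum. The 95% half-widths are then about 1.96 × 0.05 = 0.10 to 1.96 × 0.19 = 0.37 logit, against a planning value of 0.05 for the overall support effect. The causal interval may therefore be too wide to be informative, and the plan should say so in advance.
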